#### Withdrawal Criteria

Participants will be withdrawn from the study under the following circumstances: failure to use or misuse of the smart band for more than 5 consecutive days or exceeding 20% of the six-month period will result in the cessation of monitoring, with participants being notified, the device retrieved, and the data discarded. Relapse in substance use for the SUD group or the onset of addictive behavior for controls will also lead to immediate withdrawal; if the exact timing of such behavior cannot be determined, the corresponding data will be excluded. Finally, participants who voluntarily drop out of the study or request the removal of their data will be withdrawn, and their data will be discarded.

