Machine learning (ML) has also been used as a tool for the diagnosis of anxiety disorders with the use of speaking patterns, gaming activities, and self-reports [40-49]. It has also allowed researchers to measure the severity and variability of that disorder in varying environments through wearables, allowing remote intervention and through simulations [30,48,50-52]. It has also been used in predictive models for early depression diagnosis through smartphone use, severity, and progression through physical activity, sleep, and social interaction data [53-61]. In addition, ML models (MLM) have been trained to detect relapse in MDD and risk of suicide [62-64]. Similarly, it has been used to predict the start of a psychotic episode 5 days before it by using patterns of movement and sleep disturbance [63,65].

With a 60% relapse rate, an average of 5 recovery attempts required for full remission, and a growing number of new patients with SUD presenting at younger ages [2], this disorder represents a significant opportunity for digital health technologies. These tools, often used in managing cognitive and mood disorders commonly comorbid with SUD, have the potential to enhance treatment effectiveness and reduce relapse rates.

This study aims to integrate physiological, behavioral, and psychological data through digital technologies to develop comprehensive digital profiles of individuals with SUD. These profiles will be analyzed using ML tools to identify clinically relevant patterns. The resulting models are intended to serve as complementary tools in clinical practice, supporting treatment decisions, improving prognostic accuracy, and facilitating the monitoring of patients in remission.

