### Timeline

This study will include 2 types of observations: continuous passive monitoring and active surveys conducted at specific time points. Passive monitoring will occur continuously for 6 months in both groups, followed by an additional year for participants with SUD after their discharge from the treatment facility. Active surveys will be conducted at three time points: (1) baseline session or baseline, (2) 3 months after baseline, and (3) 6 months after baseline.

For digital monitoring purposes, smart bands provided to participants will be synchronized with a smartphone at the baseline session. Psychological assessment will be conducted within the first 15 days after baseline. Retesting will take place during the 15 days prior to the 6 months after baseline. Emotional reactions to cravings will be assessed at two points: (1) 3 months after baseline and (2) at 6 months after baseline (Figures 1A-1F).

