### Digital Measurement of Biomarkers

The Xiaomi Redmi Smart Band 8 will be worn on the user's nondominant hand, positioned 2 cm below the wrist bone and secured at a comfortable level, as instructed by the user manual. The device will be worn for a minimum of 22 hours per day, allowing for an anticipated loss of up to 2 hours of data due to activities such as recharging the device, synchronization with a smartphone, showering, and other routine tasks.

Physiological data, including heart rate (HR), peripheral capillary oxygen saturation, physical activity, stress, and sleep, will be collected using the device's shortest available measurement intervals. Data will capture periods of both high and low activity, during self-reported exercise, regular physical activity, and rest, and will identify any abnormalities in activity patterns.

Data synchronization, which facilitates upload to the associated Xiaomi account, will occur every 72 hours for all participants during the 6- or 18-month study period, as applicable. This data will be downloaded, preprocessed, and stored securely on an encrypted external hard drive and the institution's server for access by authorized research staff within 48 hours (Figures 2A-2E). Participants will receive a reminder notification if synchronization is not completed within 5 days.

Raw data will be used to compute digital the physiological features proposed in a MLM study by Rykov et al, [30] (Table 2).

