### Data Exclusion

Missing data will be addressed through imputation. If more than 20% of daily data samples are missing, they will be excluded. For missing data below this threshold, linear interpolation and neighbor mean imputation (k-nearest neighbor) will be applied during preprocessing using MATLAB.

The quality of data collected from the smart band will be assessed by correlating heart rate at randomly selected timestamps with oxygen saturation, activity levels, self-reported exercise, and sleep type during sleep hours. If atypical correlations are identified, 10 data points before and after the anomaly, along with 5 additional randomly chosen timestamps, will be reviewed. A day with more than 20% of faulty measurements will be excluded from the dataset.

Data will also be excluded in cases of device misuse, such as exchanging the device with other participants or nonparticipants, switching the wearing side without prior notice, or removing the device for more than 5 hours without informing the research team.

If the total sum of missing and excluded data exceeds 20% of the 6-month period, the participant's data will be removed from the study. Finally, for SUD participants, any measurements obtained during periods of substance use will be excluded, and their participation in the study will be terminated.

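### The 5-day band non-use rule has no time window, so one late gap can remove an SUD participant's completed six-month data, while controls are exposed for six months only

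*Protocol article*

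**What the plan says.** Withdrawal Criteria sets one band rule for both groups. It is triggered by "failure to use or misuse of the smart band for more than 5 consecutive days or exceeding 20% of the six-month period", and a breach "will result in the cessation of monitoring, with participants being notified, the device retrieved, and the data discarded". The second limit names a reference period; the first does not.

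The groups are monitored for different lengths of time. Timeline states: "Passive monitoring will occur continuously for 6 months in both groups, followed by an additional year for participants with SUD after their discharge". Digital Measurement of Biomarkers confirms that band data keep flowing for the longer period, since synchronization "will occur every 72 hours for all participants during the 6- or 18-month study period, as applicable".

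Data Exclusion repeats only the percentage limit, again against six months: "If the total sum of missing and excluded data exceeds 20% of the 6-month period", the participant's data are removed. Neither section gives a compliance limit for the post-discharge year, confines the 5-day limit to the first six months, or says that a completed six-month record survives a later breach.

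**The concern.** An SUD participant is exposed to the 5-day limit for three times as long as a control. If the limit runs for the whole monitored time, identical wearing behaviour removes more SUD participants than controls.

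What is lost matters as much as how many. A gap at month 15, for example, comes long after the month 0-6 record is complete and when the therapy-duration label may already be known. The stated consequence is still withdrawal with the data discarded. Months 0-6 are the only band window common to both groups, and the digital phenotype and the classifier of SUD against healthy individuals (Outcomes) both depend on group comparison. The retained SUD participants would be those who also wore the band well for up to a further year, a condition never imposed on controls. The SUD group must also supply every case for the five output categories, so each discarded record costs the prognostic models too.

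**Working it through.** **The plan's own figure.** There is none to reproduce: the article states no expected rate of band non-use or of withdrawal. The rates below are assumptions, shown as a range.

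**Inputs from the article**
- Monitoring: 6 months for controls, 6 + 12 = 18 for SUD participants (Timeline).
- Minimum of 25 per group (Sample Size), used only to turn percentages into people.
- Relapse also ends participation: "Relapse in substance use for the SUD group or the onset of addictive behavior for controls will also lead to immediate withdrawal" (Withdrawal Criteria).
- Background relapse: "With a 60% relapse rate" (Introduction), with no time frame attached. Placing it in the post-discharge year is an assumption.

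**Step 1. The 5-day limit running for the whole monitored time.** Let p be the chance of at least one gap of more than 5 days in six months, with the same constant hazard in both groups and independent periods. Controls lose p. SUD participants lose 1 − (1 − p)³.

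| p | Controls lost | SUD lost | Ratio | Kept of 25: controls / SUD |
|---|---|---|---|---|
| 5% | 5% | 1 − 0.95³ = 14.3% | 2.85 | 23.75 / 21.4 |
| 10% | 10% | 1 − 0.90³ = 27.1% | 2.71 | 22.5 / 18.2 |
| 20% | 20% | 1 − 0.80³ = 48.8% | 2.44 | 20 / 12.8 |

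The difference between the two loss columns (9.3, 17.1 and 28.8 percentage points) is the share of SUD participants who had passed the 5-day limit throughout months 0-6 and are removed only for a later gap. Of 25, that is about 2.3, 4.3 and 7.2 people.

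**Step 2. Relapse as a competing exit.** A participant who relapses is no longer at risk of a band breach. Take h = −ln(1 − p)/6 per month for a gap and λ = −ln(1 − 0.60)/12 = 0.0764 per month for relapse after discharge. SUD loss to the band rule is then

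p + (1 − p) × [h/(h + λ)] × [1 − exp(−12(h + λ))].

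For p = 10%: h = 0.0176, h/(h + λ) = 0.187, and exp(−12(h + λ)) = 0.90² × 0.40 = 0.324. The loss is 0.10 + 0.90 × 0.187 × 0.676 = 21.4%.

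| p | SUD lost, 60% relapse | Ratio to controls |
|---|---|---|
| 5% | 11.1% | 2.2 |
| 10% | 21.4% | 2.1 |
| 20% | 39.5% | 2.0 |

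With 40% relapse the losses are 12.3, 23.5 and 43.0%; with 80% they are 9.7, 18.7 and 35.1%.

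**Step 3. The 20% limit.** Both places that state it refer to the six-month period, which both groups complete. Equal behaviour in that period gives equal removal, so this limit adds no difference.

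**Step 4. Both limits confined to months 0-6.** Exposure is then the same in the two groups, and the ratio of losses for equal behaviour is 1.0.

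**The case against.** The strongest reply is that the two limits share one clause and the only period named there is six months. If both belong to that period, the groups are treated alike. That reading is possible, but the text does not state it, and band monitoring of SUD participants plainly continues to month 18.

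A second reply is that the article does not specify which data go after a late breach, and that Data Exclusion ties removal of a participant's data to the 20% limit, not to a 5-day gap. This is fair: loss of the whole record is the literal reading, not an explicit statement. But the relapse clause in the same section narrows the exclusion to the affected data when timing is unknown, and the band clause carries no such restriction.

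Third, the size rests on assumptions. Non-adherence that clusters within persons would lower the 18-month figure, and relapse shortens time at risk. Both points stand. Nor do the documents show that wear is unsupervised after discharge, since synchronization continues and reminders are sent.

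Fourth, a condensed article may leave such detail to the full protocol. Here, however, the rule and its consequence are stated, and they do not fit the stated follow-up.

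**Conclusion.** The point holds for the 5-day limit. It has no window, it ends in withdrawal with data discarded, and SUD participants are exposed to it for up to 18 months against 6. Taken literally, it makes inclusion in the month 0-6 comparison depend on later adherence in one group only. For assumed six-month gap probabilities of 5 to 20%, SUD losses are about 2 to 3 times control losses: 14/27/49% against 5/10/20%, or about 11/21/40% with 60% relapse as a competing exit. The sizes depend on an equal constant hazard and independent periods. The direction needs only some chance of a gap after month 6 and similar behaviour before it.

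Two stronger conclusions are not supported. A reader might infer that the 20% allowance is also stricter for SUD participants, because missing days would accumulate over 18 months against a six-month denominator. No section says so, and the plain wording refers to a period both groups share. A reader might also suppose that the losses fall on an already smaller group. The article plans a 1:1 ratio and reports 18 SUD participants and 17 controls enrolled as of June 2025.

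**What to change.** In Withdrawal Criteria and Data Exclusion:

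1. Apply the 5-day and 20% limits to months 0-6, identically in both groups.
2. Assess band compliance in the SUD post-discharge year separately, with its own denominator.
3. State that a breach in that year removes only post-discharge band data. Month 0-6 band data, psychological and craving data, and outcome labels are kept unless the participant requests removal.

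The cost is wording in two sections. The downside is that some SUD participants will have band data for the first window only. Enrolment is under way and discarded data may not be recoverable, so the change is best made before the first SUD participants are far into the post-discharge year.

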## Methods

### Goal and Objectives

The purpose of this study is to develop and validate a predictive model of substance use relapse or rehabilitation with ML in patients with SUD. This will be through using digital physiological measurements (digital biomarkers), demographic and psychological profiles, automatic facial emotion recognition, and the emotional state during craving (ESDC).

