**Figure 5 figure5:**
[figure not shown]
Model’s possible outputs. These categories will be used as output labels of the predictive model and will allow the evaluation of the patterns detected from the input.

For the duration of the therapeutic process, the following labels will be used:

Timely rehabilitation: patients with SUD who complete the rehabilitation protocol within 7 months.Late rehabilitation: patients with SUD who complete the protocol in 7 months or longer.

Regarding relapse latency, the labels will include the following:

Early relapse: substance use occurring within the first 6 months post discharge.Late relapse: substance use occurring after 6 months but before the completion of 18 months post discharge.One-year maintenance: patients who have abstained from substance use at the end of the 18-month postrecovery period.

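### Relapse is the outcome to be predicted, but the withdrawal and exclusion rules do not say that relapsers keep their label and earlier data, and some of them can selectively remove relapsers

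*Protocol article*

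**What the plan says.** Goal and Objectives sets the aim: to "develop and validate a predictive model of substance use relapse or rehabilitation with ML in patients with SUD". The labels under Output include two relapse classes, both counted from discharge: "Early relapse: substance use occurring within the first 6 months post discharge" and "Late relapse: substance use occurring after 6 months but before the completion of 18 months post discharge". The third latency label is maintained abstinence.

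Withdrawal Criteria sets these rules:

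- **Relapse:** "Relapse in substance use for the SUD group or the onset of addictive behavior for controls will also lead to immediate withdrawal".
- **Undated use:** "if the exact timing of such behavior cannot be determined, the corresponding data will be excluded".
- **Non-wear or misuse:** monitoring stops and the data are discarded on "failure to use or misuse of the smart band for more than 5 consecutive days or exceeding 20% of the six-month period".
- **Drop-out:** data are discarded both for those who leave voluntarily and for those who ask for removal. The two are joined by an 'or', so leaving without any such request is enough.

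Data Exclusion adds, for the SUD group, that "any measurements obtained during periods of substance use will be excluded, and their participation in the study will be terminated".

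Neither section says whether a withdrawn relapser stays in the modelling data with the relapse label, and neither sets separate rules for the year after discharge.

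**The concern.** The same event is a model output and a ground for leaving the study. That is workable if relapse simply ends follow-up and the record is kept, but the article does not say so. Staff who follow the withdrawal rules literally could drop the cases that the model must learn from.

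The undated-use rule is the clearest problem, because among SUD participants it can act only on people who have the outcome. Discarding the records of non-wearers and drop-outs adds to the selection if those behaviours go with relapse, which is plausible but not quantified in the article.

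At stake are the number of relapse cases available for training and testing, and whether performance measured in adherent participants carries over to the patients for whom the interface is intended. Discarded data cannot be recovered later.

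**Working it through.** **Step 1: the rules set against the labels.**

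| Trigger | Stated consequence | Who can trigger it (SUD group) | What the label needs |
|---|---|---|---|
| Dated relapse | Withdrawal; use-period measurements excluded | Relapsers only | Date is known, so the class can be assigned; retention of label and earlier data not stated |
| Undated use | Associated data excluded | Relapsers only | Only whether use fell before or after 6 months from discharge |
| Non-wear or misuse | Monitoring stops; data discarded | Anyone | Outcome status does not depend on the band record |
| Voluntary drop-out | Data discarded | Anyone | Status up to last contact |

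The second row selects on the outcome by construction. The third and fourth do so only if the behaviour differs between relapsers and abstainers.

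**Step 2: inputs for a size.**

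- Relapse rate 60% (Introduction; a general background figure).
- SUD participants: 25 (Sample Size; a minimum per group).
- Loss rates: none are given. Let q be the share of relapsers lost and r the share of abstainers lost. Both are assumptions.

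**Step 3: with nothing lost.** Relapsers 0.6 × 25 = 15; abstainers 0.4 × 25 = 10.

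**Step 4: with loss.** Relapse share = 0.6(1 − q) / [0.6(1 − q) + 0.4(1 − r)].

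With r = 10%, abstainers kept = 10 × 0.9 = 9.

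| q | Relapsers kept | Total kept | Relapse share |
|---|---|---|---|
| 25% | 15 × 0.75 = 11.25 | 20.25 | 55.6% |
| 50% | 15 × 0.50 = 7.5 | 16.5 | 45.5% |
| 75% | 15 × 0.25 = 3.75 | 12.75 | 29.4% |

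With r = 0, the same values of q give 11.25/21.25 = 52.9%, 7.5/17.5 = 42.9% and 3.75/13.75 = 27.3%.

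**Step 5: equal loss as a check.** With q = r = 20%, 12 relapsers and 8 abstainers remain: 12/20 = 60%. The shift in share comes entirely from the difference between q and r.

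**Step 6: per class.** If relapses split evenly between early and late (a further assumption), 7.5 kept relapsers are 3.75 per class, before the division into training, validation and test folds described under Data Preprocessing.

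**The case against.** The strongest reply is that Withdrawal Criteria uses different words for different triggers. Data are discarded for non-wear and drop-out; relapse brings withdrawal, and exclusion follows only if the timing is unknown. Data Exclusion likewise removes only measurements taken during use. A reader might infer that every relapse is deleted, but the text does not support this: a dated relapse can be labelled and its earlier data used. This part of the reply stands, and for dated relapse the need is an explicit statement, not a reversal.

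Other stronger readings also go beyond the text:

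- **The 5-day limit running through all 18 months.** No period is stated for it, and the 20% limit in the same sentence refers to six months. If the 5-day limit also stops at six months, a relapse after discharge cannot be what caused the non-wear.
- **A warning that comes too late.** The article says "Participants will receive a reminder notification if synchronization is not completed within 5 days". That concerns synchronization, not wear, so it says nothing about how non-wear is followed up.
- **The meaning of excluded data for undated use.** It may be the affected measurements or the whole record. The wording leaves this open, which is itself a reason to settle it.
- **An underestimated relapse rate.** Estimating that rate is not an objective. A change in class share alone does not bias the AUC either, though it does move F2. Bias in the AUC would need selection within classes, which is possible but not shown.
- **Missing classes for use before discharge or non-completion.** The Predictive Model section limits sobriety prediction to people rehabilitated at the centre, so these may be out of scope by design.

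The 60% is not this centre's rate, 25 is a minimum that the study aims to exceed, and the loss rates are assumed. All of that is fair. It limits what can be said about size but leaves the gap in the rules untouched.

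**Conclusion.** The point holds in a limited form. Relapse is both the target and a ground for withdrawal, and the article does not say that label and pre-relapse data are retained. The undated-use rule acts only on relapsers within the SUD group and asks for more precision than the labels require. Discarding the data of non-wearers and of drop-outs who made no removal request can add to the selection.

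The effect cannot be sized from the article. Under the assumed losses of 10% of abstainers and 25% to 75% of relapsers, the relapse share falls from 60% to between 56% and 29%, and relapsers from 15 to between about 11 and 4. With equal loss the share does not move, although the number of cases still falls. The direction rests on the undated-use rule and on the plausible, unquantified link of non-wear and drop-out with relapse.

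**What to change.** Reconcile Withdrawal Criteria and Data Exclusion with the labels under Output:

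1. State that relapse is an endpoint: it ends follow-up, and the label and all data collected before it are kept.
2. Assign undated use to a relapse class from the interval between last known abstinence and first known use. If that interval spans the 6-month cut, treat it as interval-censored.
3. Let non-wear mask or end only the wearable stream, keeping demographic, psychological and outcome data, and state the period to which the 5-day limit applies.
4. Discard a participant's data only when removal is requested, within the consent terms.

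The cost is amended wording and more incomplete wearable records to handle in the analysis. As of June 2025, 18 SUD participants were enrolled and recruitment was planned to January 2027, so an early change protects most of the data. Extra labels for use before discharge or non-completion, and a discrete-time survival model for latency, are optional.
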